### Data collection and monitoring

2.8

During the screening visit, the subjects will fill out a questionnaire about their sociodemographic characteristics, provide a medical history of the last 6 months and drug history of the last 4 weeks, and have x-rays of the knee and laboratory tests performed. Personal information and data collected during the screening period will be managed by the hospital. The monitoring of data and research performance will be performed regularly by Jeneolurl Bio Taek Co., Ltd. (Pusan South Korea). The final exam dataset will be accessible to statisticians and key investigators. The results of this study will be published in a peer-reviewed journal.

### Statistical analysis

2.9

Statistical analysis will be performed on the principle of full analysis set. For the Intention to Treat analysis, missing values will be analyzed by last observation carried forward. The baseline values before treatment and the changes in K-WOMAC at 4 and 8 weeks after treatment will be measured for each of the 2 experimental groups and the control group. To test the difference between two groups of continuous variables, an independent *t* test will be performed if the data follow a normal distribution. If not, Mann-Whitney *U* test will be performed. Paired *t* tests will be performed if the data follow a normal distribution to test the differences between groups. If not, Wilcoxon's signed-rank test will be performed. The test of normality for continuous variables will be analyzed using the Shapiro-Wilk's test. The confidence level will be set at 5%. All statistical analyses will be performed using SPSS Statistics for Windows Version 20.0 (IBM Corp., Armonk, NY).

Drinking, which can affect the weekly evaluation, is considered a management variable, and if there is a difference between groups, analysis of covariance will be performed. Descriptive statistics such as number of subjects, mean, standard deviation, minimum, median, maximum will be presented for baseline, each visit, and final evaluation, as will changes from baseline to final evaluation for continuous data, clinical laboratory tests, and vital signs. For categorical data, a division table will be provided. If necessary, 95% confidence intervals will be calculated. No intermediate analysis will be performed.

Demographic variables measured at the screening visit will be summarized for each treatment group. Assays for comparison of drug administration groups will be performed. The continuous data will be tested using the *t* tests or Wilcoxon's rank sum test. Categorical data will be analyzed using a chi-square test or Fisher exact test.

The safety assessment calculates the rate of adverse events. Continuous data such as comparisons between groups, individual laboratory test results, and biomarkers will be analyzed using paired *t* tests or t-tests with 95% confidence intervals within the group to see if there are any changes compared to the baseline. If the distribution is not normal, nonparametric statistics (Wilcoxon signed rank test or Wilcoxon rank sum test) will be performed. Categorical data are presented as frequencies and ratios for each parameter. The difference between groups will be analyzed using the chi-square test and Fisher exact test.

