### Sample size calculation

2.4

The optimal sample size for the preliminary study and parallel design is 8 people per group. To ensure the feasibility of determining mean and variance with appropriate precision, the total sample size was maintained at 24 and divided into 3 groups.^[7]^ The pilot study will be conducted after the recruitment of 24 subjects (8 per group) who meet the selection criteria.

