### Randomization and blinding procedures

2.5

To conduct this clinical study scientifically and objectively, the final selected subjects are assigned in a ratio of 1:1:1 to experimental groups 1, 2 and a control group using block randomization. The size and number of blocks for randomization are set by the statistician and remain unknown to the researchers. The total random code is generated at about 120% of the target population. The randomized code of 3 digits (eg, PLA-R-001, PLA-R-002, PLA-R-024) is assigned in order of recruitment according to the randomization details. The test compound or placebo, packaged according to the code, is given to the subject. The randomized code cannot be used again even if the target of the randomized code is dropped. Randomization details are generated by statisticians using nQuery Advisor 7.0 (or SAS 9.0 or SPSS 21.0) and sent to the drug manufacturer. The statistician seals the randomized data for each subject in a secure envelope and sends it to the research institution.

To maintain the double-blinding, the placebo and active ingredient are identical and cannot be distinguished by appearance by the participants or staff. The code assigned to subjects will be kept sealed and will not be released until the end of the clinical trial. Cases in which the blinding must be unsealed, such as a serious adverse drug reaction, will be managed using a separate envelope created for each subject so that only their randomization is revealed. Randomization and blinding will not be revealed to the researchers until the end of the study.

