### Intervention

2.6

All participants in the study will receive PL 1000 mg, PL 1500 mg or placebo with water 30 minutes after meals, 3 capsules, twice-daily will be taken for 8 weeks. Subjects will be assessed twice in 8 weeks, at 4 weeks and 8 weeks. The capsules will be produced by Hankookshinyak Pharmaceutical Co. (Nonsan, Republic of Korea).

Any treatment already being taken at the time of the trial or any dietary supplements taken and any additional treatments during the trial will be considered combination therapy. If coadministration is necessary, the details of the administration will be recorded on the case record and subject chart. We will try to avoid any changes to the combination therapy during the trial. Administration of concomitant medications will be minimized during the trial and will be allowed only if it is necessary for the welfare of the subject and it is determined that it will not affect the study according to the judgment of the study personnel. If a surgical operation that does not violate the objectives of this study is performed during the trial, it will be noted on the adverse event page of the case record. The symptoms of overdose in humans are not known, but treatment and other drugs will be provided if adverse reactions or an overdose occurs. Eligible subjects may be dropped if any of the following occurs: violation of inclusion/exclusion criteria, subject requests to withdraw from the study; a serious adverse event or an adverse reaction that makes it difficult to continue; a major violation of the protocol (the use of a prohibited substance, a drug or functional food), or any consumption which may affect the trial or endpoint; subjects become pregnant during the trial. In all cases of dropout, the cause shall be documented in detail in the case record and clinical laboratory tests will also be conducted as a safety assessment. If an adverse reaction occurs, follow-up observation will proceed until the cause of the adverse reaction is identified. The results will be reported in accordance with safety evaluation criteria, evaluation methods and reporting protocols for adverse reactions. The Institutional Review Board will be notified immediately if a subject drops out due to a serious adverse event that is life-threatening, requires hospitalization or prolongation of hospitalization, causes persistent or meaningful disability or dysfunction, congenital malformation, abnormality, medically critical condition, or death.

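### Last observation carried forward is the only stated handling of missing values, so a late dropout's week-4 K-WOMAC change is analysed as week 8, which can bias the dose-placebo difference

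*Protocol article*

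**What the plan says.** Protocol article, section 2.9 (Statistical analysis): "Statistical analysis will be performed on the principle of full analysis set". The next sentence adds that, in the intention-to-treat analysis, "missing values will be analyzed by last observation carried forward". The primary variable is the change in K-WOMAC at weeks 4 and 8, compared by t test or Mann-Whitney test. No second missing-data method and no sensitivity analysis is named.

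Section 2.6 (Intervention) gives the visits: "Subjects will be assessed twice in 8 weeks, at 4 weeks and 8 weeks". Section 2.1 agrees. Section 2.7 (Outcome measures) differs and adds an outcome evaluation at week 12.

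Section 2.4 (Sample size calculation) plans "the recruitment of 24 subjects (8 per group) who meet the selection criteria", as a pilot rule and not a power calculation. No dropout rate, SD or expected effect is given.

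Section 2.10 (Withdrawal and dropout) says that subjects who withdraw consent, or who turn out not to meet the criteria, are excluded from the study. It does not say whether they also leave the analysis.

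**The concern.** Carrying a score forward assumes that it would have stayed put. In an 8-week trial of a product meant to improve symptoms, the scores are expected to move. A week-4 change labelled as week 8 is then the wrong quantity for that subject.

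If loss is unequal between arms, the error does not cancel. Loss from an improving PL arm understates the benefit, and loss from an improving placebo arm overstates it. Section 2.6 lists reasons for leaving that could differ by arm, such as adverse reactions and use of a prohibited drug or functional food.

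The tests also count each filled value as a real week-8 observation. Section 2.4 justifies the arm size by the wish to determine mean and variance with suitable precision. LOCF can distort both, and the distortion would pass into the planning of a follow-up trial.

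**Working it through.** **The plan's own figure.** 3 arms x 8 = 24, as stated. There is no power calculation to reproduce. One subject is 1/8 = 12.5% of an arm.

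**Inputs.** From the article: 8 per arm (2.4), assessments at weeks 4 and 8 (2.1, 2.6, 2.9), LOCF (2.9). Assumed, because the article gives none: mean improvement of 4 points by week 4 and 8 points by week 8, and the dropout numbers below.

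**Shift in an arm's mean.** Shift = (number lost / 8) x (true week-8 change - carried change).
- One lost after week 4: 1/8 x (8 - 4) = 0.5 point.
- One lost before week 4, if baseline is carried: 1/8 x (8 - 0) = 1.0 point.
- Two of either kind: 1.0 and 2.0 points.
- None lost: 0.

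If loss is in one arm only, the whole shift goes into the dose-placebo difference. If both arms lose the same number, what remains is the difference between the two arms' shifts.

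**Simulation under stated assumptions.** 40,000 trials per scenario; two arms of 8; pooled t test at two-sided 0.05 on week-8 change; SD 1 at each visit; correlation 0.5 or 0.7; random loss; baseline carried for early loss. The comparator uses observed week-8 values only and is unbiased here because loss is random. Where a true difference of -0.80 SD was set, placebo improved by 0.4 SD and the active arm by 1.2 SD.

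| Loss | LOCF estimate of -0.80 | Coverage of the 95% interval |
|---|---|---|
| None | -0.80 | 95% |
| 12% in both arms | -0.73 | 95% |
| 25% in both arms | -0.65 to -0.60 | 92 to 94% |
| 25% in the active arm only | -0.58 to -0.50 | 88 to 93% |

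Two rows can be checked by hand. With 25% early loss in both arms, -0.80 + 0.25 x 0.80 = -0.60. With 25% early loss in the active arm only, -0.80 + 0.25 x 1.2 = -0.50.

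With no true difference, both arms improving by 0.8 SD and 25% loss in one arm, type I error was 6.3 to 8.9%. With equal loss and no true difference it stayed near 5%.

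**Standard error.** In these scenarios the LOCF standard error was about 4 to 27% below that of the observed-data analysis. This is not general. Take six observed values averaging 8 with SD s, plus two zeros. The mean is 6, and the expected sum of squares is 5s² + 6 x (8 - 6)² + 2 x (0 - 6)² = 5s² + 96, so the expected variance is (5s² + 96)/7.
- LOCF squared SE: (5s² + 96)/56.
- Six-subject squared SE: s²/6.
- LOCF is smaller only if 30s² + 576 < 56s², that is s² > 576/26 = 22.2, or s > about 4.7 points.

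For a smaller s, the zeros widen the interval instead.

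**The case against.** **Early dropouts may never be filled in.** Section 2.9 does not say that baseline is carried forward, and the full analysis set is not defined in the article. If the set requires a post-baseline score, or if section 2.10 means exclusion from the analysis, the 1.0-point figure does not arise. This stands, so that figure is conditional. The late-dropout shift is not affected.

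**The size is unknown.** No dropout rate is stated, differential loss is a possibility and not a fact, and with equal loss and no true effect the test keeps its level. This stands too. Bias arises at any sample size; arms of 8 only give each subject more weight.

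**A reader might infer a fixed shrinkage of the standard error**, for example by the factor sqrt(6/8) for two dropouts. That assumes filled values with the same mean and spread as the observed ones. The calculation above shows that the standard error can move either way, and the article gives no SD to settle it. The t-test standard error also matches the sampling spread of the LOCF estimate itself; what is wrong is its relation to the true week-8 difference.

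**A reader might infer that K-WOMAC is not taken when a subject leaves.** On dropout, section 2.6 says "the cause shall be documented in detail in the case record and clinical laboratory tests will also be conducted as a safety assessment". The word also does not limit the assessment to laboratory tests, and the visit schedule in Table 2 is not shown. The document does not support that reading.

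**The choice may be left to a fuller plan.** This does not stand for LOCF itself, which the article fixes.

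**Conclusion.** The point holds. LOCF is the sole stated method, and under the week-4 and week-8 schedule it presents a late dropout's week-4 change as week 8. If scores move and loss differs by arm, the dose-placebo difference is biased, in a direction that depends on which arm loses subjects. LOCF therefore cannot be defended as safely conservative.

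Under the assumed 4-point and 8-point improvement, the shift is 0.5 point in an arm's mean per late dropout, 1.0 point per early dropout if baseline is carried, and nil without dropout. The real size cannot be given, because dropout, trend and SD are all unstated. No general figure for the error in the standard error is supported. The plan should be changed, but the documents do not show that the trial's result will be materially wrong.

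**What to change.** 1. Make the main K-WOMAC analysis a mixed model for repeated measures on the observed week-4 and week-8 values, with treatment, visit, treatment-by-visit, baseline, unstructured covariance and small-sample degrees of freedom. Multiple imputation is an acceptable alternative.
2. Keep LOCF only as a sensitivity analysis.
3. State whether subjects without a post-baseline score belong to the full analysis set, and reconcile the exclusion of withdrawn subjects in section 2.10 with the intention-to-treat wording in section 2.9.
4. Reconcile the week-12 evaluation in section 2.7 with sections 2.1, 2.6 and 2.9. If week 12 is real, week-8 scores could also be carried forward.

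**Cost.** No new data are needed. The change replaces the t test or Mann-Whitney test as the main K-WOMAC comparison, so it is more than a change of wording. Two visits need only three covariance parameters, which is workable with 24 subjects. The model assumes data missing at random and gains no outcome information from a subject with no post-baseline score, so the number of such subjects should be reported by arm.

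### K-WOMAC changes are compared without adjusting for the baseline K-WOMAC that is collected: valid, but on average less precise than a baseline-adjusted model, by an amount the document does not let one fix

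*Protocol article*

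**What the plan says.** Section 2.9 (Statistical analysis) states: "The baseline values before treatment and the changes in K-WOMAC at 4 and 8 weeks after treatment will be measured" for both experimental groups and the control group. So every subject is to have a baseline value and changes at weeks 4 and 8.

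For the comparison the section says: "To test the difference between two groups of continuous variables, an independent" *t* test is used when the data are normal, and a Mann-Whitney *U* test otherwise. The rule that decides is also given: "The test of normality for continuous variables will be analyzed using the Shapiro-Wilk's test". No covariate is attached to the K-WOMAC comparison, and no model covering all three arms appears. Analysis of covariance is mentioned once, for drinking, and only if the groups differ on it. Confidence intervals are to be calculated only where necessary.

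Section 2.4 (Sample size calculation) states "The optimal sample size for the preliminary study and parallel design is 8 people per group" and gives the reason as "To ensure the feasibility of determining mean and variance with appropriate precision". No effect size, SD or power is given.

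**The concern.** Section 2.4 justifies 8 per arm by precision, so precision is what this pilot has to protect. A change score subtracts the whole baseline value, which is the best use of baseline only when the slope of follow-up on baseline equals 1. At any smaller slope, change is negatively related to baseline by regression to the mean. An arm that starts worse by chance then appears to improve more.

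With 8 per arm such chance differences are not small. The covariate that would deal with them is already collected, and the plan already contains the method (analysis of covariance) but uses it for another variable. Because the article names the tests, the rule that selects them and the one trigger for covariance adjustment, this is a stated choice and not detail left to a fuller document.

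**Working it through.** **Inputs from the document.** There are 8 subjects per arm and 3 arms (section 2.4: "the total sample size was maintained at 24 and divided into 3 groups"), allocated 1:1:1 (section 2.5). Section 2.9 says "The confidence level will be set at 5" per cent, read here as a two-sided 5% significance level. There is no stated effect, SD or power to reproduce; 3 × 8 = 24 is consistent.

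**Assumed, because not given.** The baseline-to-follow-up correlation ρ is taken from 0.3 to 0.9. The ratio *k* of follow-up SD to baseline SD is taken as 1, then varied. Units are baseline SDs, and the data are taken as normal.

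**Half-width of the 95% interval for one dose against placebo, *k* = 1.**

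- Change-score *t* test on two arms (14 df): 2.145 × √(2(1−ρ)) × √(2/8).
- Three-arm model with baseline as covariate (20 df): 2.086 × √(1−ρ²) × √(2/8) × √(1+1/19). The last factor is the expected cost of chance baseline imbalance.

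| ρ | Change score | Adjusted | Narrower by |
|---|---|---|---|
| 0.3 | 1.27 | 1.02 | 20% |
| 0.5 | 1.07 | 0.93 | 14% |
| 0.7 | 0.83 | 0.76 | 8% |
| 0.8 | 0.68 | 0.64 | 5% |
| 0.9 | 0.48 | 0.47 | 3% |

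A simulation of 6,000 trials per scenario gave mean width ratios of 0.81, 0.87, 0.92, 0.95 and 0.97 to 0.98, in agreement. In single trials the adjusted interval was the narrower one in about 88%, 80%, 72%, 66% and 60% of cases.

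**Where the gain comes from.** Moving from 14 to 20 df gives 2.086/2.145 = 0.973. The imbalance cost is √(20/19) = 1.026. Their product is 0.998, so the two cancel. The rest is √((1−ρ²)/(2(1−ρ))) = √((1+ρ)/2), which is the covariate alone.

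**Unequal SDs.** The variance of change is 1 + k² − 2ρk and the adjusted residual variance is k²(1−ρ²). The difference is (1−ρk)², which is never negative and vanishes when the slope ρk equals 1.

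- k = 1.3, ρ = 0.7: 0.870 against 0.862; 0.998 × √(0.862/0.870) = 0.993, about 1% narrower.
- k = 1.3, ρ = 0.5: 1.390 against 1.268; ratio 0.953, about 5% narrower.
- k = 0.8, ρ = 0.7: 0.520 against 0.326; ratio 0.79, about 21% narrower.

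**Chance imbalance.** The baseline difference between two arms of 8 has SD √(2/8) = 0.5, so about 32% of contrasts exceed 0.5 SD in either direction. With k = 1, the change-score contrast carries (1−ρ) times that difference, with opposite sign. At ρ = 0.5, an imbalance of 0.5 SD shifts the estimate by 0.25 SD.

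**Normality pre-test.** With 8 values, Shapiro-Wilk at 5% rejected exponential data in about 34% to 35% of samples and chi-square (4 df) data in about 18%. With truly normal data, testing both arms sends 1 − 0.95² = 9.75% of comparisons to Mann-Whitney (about 10% in simulation). Type I error of the whole two-step procedure under normality was 0.047 to 0.056.

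**The case against.** The strongest reply is that this is a matter of efficiency and not an error. That stands. Under randomisation the change-score comparison is unbiased over repeated trials and holds its type I error. Baseline imbalance shows up as extra variance, and as a shift only within the particular trial. A reader might infer from the missing covariate that the planned test is biased or invalid; the document does not support that.

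A reader might also infer that adjustment would give clearly narrower intervals whatever the data. That does not follow. The gain depends on two quantities the document does not give, it falls to a few per cent at high correlation or when the slope is near 1, and it is an average that does not hold in every data set.

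Three further limits stand. First, using 16 of 24 subjects for each error estimate looks wasteful, but the df gain is cancelled by the cost of the covariate. Second, the pre-test hardly moves type I error under normality, and the promised descriptive statistics leave a mean change to the final evaluation recoverable whichever test is run, so the pre-test is a secondary matter. Third, the document gives no distribution for any biomarker, so it offers no ground for prescribing a log scale. Power for a chosen effect is left out as well, since the trial sets no effect size.

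What the reply does not remove is that the adjustment uses data already collected and, under the working assumptions, is on average at least as precise at every correlation and SD ratio examined.

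**Conclusion.** The point holds as an avoidable loss of precision in a valid analysis. With equal SDs at baseline and follow-up, the expected 95% interval would be about 20% narrower at a correlation of 0.3 and about 3% narrower at 0.9. With a follow-up SD 1.3 times baseline, the gain is about 5% at correlation 0.5 and 1% at 0.7; with a ratio of 0.8 it is about 21% at 0.7. The direction is secure and the size is not. Nearly all of the gain comes from the covariate.

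The figures rest on normal data, a linear baseline relation, and a common slope and residual variance across placebo and both doses. Eight per arm can hardly check that last assumption; it is the small price of the change. The benefit that does not depend on average width is that the estimate no longer carries part of a chance baseline difference.

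**What to change.** In section 2.9, make the primary analysis one prespecified linear model of week-8 K-WOMAC on treatment (three levels) and baseline K-WOMAC. Report each dose-minus-placebo difference with its 95% confidence interval as a matter of course. The treatment estimate is the same if change replaces the week-8 score, provided baseline is in the model. Use the same adjustment, each outcome with its own baseline, for the continuous secondary outcomes. State the common-slope and common-variance assumptions.

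As a secondary change, remove the Shapiro-Wilk step as the selector of the main method and keep a rank-based analysis as a sensitivity check. Both dose contrasts and both visits are then reported on one scale.

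The cost is wording only. No extra data or visits are needed, and the plan already provides for analysis of covariance. The change should be fixed in writing while the randomisation codes are still sealed.

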### Inclusion and exclusion criteria

2.2

The inclusion criteria are as follows: age, 40 to 75 years; patients with a Kellgren and Lawrence grading scale of 1 or 2 in both knee joints, (assessed on AP and lateral x-rays); those who have taken arthritis medications and have not changed their medications within the last month; applicants who have provided written consent to be a subject of this study because of the effects of KOA on their normal physical activity.

The exclusion criteria are as follows: Those who are currently being treated for clinically significant acute or chronic disorders of any of the following systems: cardiovascular, cerebrovascular, immune, respiratory, hepatobiliary, kidney and urinary, and neurological. Musculoskeletal disorders, mental, infectious or blood and neoplastic diseases. After consideration of the subject's condition, the research director may decide to allow participation in the study. A person whose arthritis is considered to be other than degenerative, as judged by the research director; a history of lower extremity fracture within the last 3 months; creatinine blood levels of more than twice the normal upper limit; patients who have received an intraarticular injection with hyaluronic acid or steroids within 3 months of the study; those whose blood levels of AST GOT or ALT GPT are more than 3 times the normal upper limit; individuals who have uncontrolled hypertension (160/100 mm Hg or more, measurement after 10 minutes at rest); individuals taking medication for a psychiatric disorder, (not including, intermittent medication for sleep disorders); individuals with a history of using herbal medicine or treatment in the last 2 weeks; patients who have received other research drugs within the last 4 weeks; patients who must continue to take drugs that are deemed to affect the results of human clinical trials; persons with a history of gastrointestinal resection (except appendectomy); those who have had artificial joint surgery; pregnant or nursing women; alcoholics or people who drink more than 4 times/week; persons with hypersensitivity to the test food or its components; any person deemed inappropriate by the research director.

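### Covariate adjustment is made to depend on an observed group difference in drinking, with neither the criterion nor the timing of the drinking measure fixed

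*Protocol article*

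**What the plan says.** Section 2.9 (Statistical analysis) compares groups by an independent t test or, if the data are not normal, a Mann-Whitney U test. It introduces this with "To test the difference between two groups of continuous variables". The only covariate rule in the article follows in the next paragraph: drinking "is considered a management variable, and if there is a difference between groups, analysis of covariance will be performed".

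The article does not say how a difference in drinking is to be judged, when drinking is measured, or which outcome the analysis of covariance covers. Elsewhere, drinking appears only in section 2.2, where the exclusions include "alcoholics or people who drink more than 4 times/week". Section 2.8 describes a sociodemographic questionnaire at screening but does not name drinking. Section 2.5 describes 1:1:1 block randomisation and mentions no stratification by drinking. Section 2.4 sets 8 subjects per group.

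**The concern.** Whether the comparison is adjusted is decided by the data. Under randomisation, a baseline difference in drinking is due to chance, so testing for it does not show whether adjustment is useful. That depends on how strongly drinking predicts K-WOMAC. With 8 per arm the check also performs poorly as a detector of imbalance. As no criterion is given, the choice could be made after the outcome data and the allocation are known.

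The second weakness is timing. The phrase "Drinking, which can affect the weekly evaluation" ties drinking to an evaluation schedule that the article does not otherwise contain, since assessments are every 4 weeks. If the covariate were drinking during treatment, a group difference could itself be a consequence of treatment, and that is when the rule would adjust for it.

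**Working it through.** **Inputs from the protocol article.** There are 8 subjects per group in three groups (section 2.4): 3 × 8 = 24, which reproduces the stated total. No power, effect size or SD is given, so there is no power figure to reproduce. The significance level is 5% (section 2.9); sidedness is not stated and two-sided is assumed.

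**Assumptions, because the article gives no values.** The trigger is a two-sided t test on drinking at 5%. One PL arm is compared with placebo, 8 vs 8. Drinking and outcome are normal with within-arm SD 1. The drinking-outcome correlation ρ is 0, 0.3, 0.5 or 0.7.

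**Model.** Drinking X = γ·arm + noise. Outcome Y = δ·arm + ρ·X + √(1 − ρ²)·noise. The total treatment effect is δ + ρ·γ. The rule uses analysis of covariance on X if the test on X is significant, and otherwise an unadjusted t test. Each scenario had 200,000 simulated trials.

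**Step 1: how often the rule fires.** For a drinking difference of d SD, the t test has 14 df and noncentrality d·√(8/2) = 2d. At d = 0 it fires in 5% of comparisons, at d = 0.5 in about 15%, and at d = 1 in 46%. A true 1 SD difference in drinking is therefore missed more often than it is found.

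**Step 2: drinking is a baseline value (γ = 0).** The mean estimate equals the true effect under every approach, so there is no bias. The other properties are:

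| ρ | Size, rule | Size, always adjusted | Power at 1 SD, rule | Power at 1 SD, always adjusted |
|---|---|---|---|---|
| 0 | 5.0% | about 5% | about 45% | 43% |
| 0.3 | 4.8% | about 5% | about 46% | 47% |
| 0.5 | 4.4% | about 5% | 46% | 54% |
| 0.7 | 3.7-3.8% | about 5% | 46% | 70% |

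The unadjusted t test has 46% power throughout. The rule stays near that figure because it adjusts in only about 1 comparison in 20.

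**Step 3: drinking is measured on treatment and PL changes it (assumed).** Take ρ = 0.5 (slope 0.5) and a direct effect δ of 0.5 SD.

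| Shift in drinking γ | Total effect δ + ργ | Rule fires | Mean estimate when it fires | Mean estimate over all trials |
|---|---|---|---|---|
| 0.5 SD | 0.5 + 0.5 × 0.5 = 0.75 | about 15% | 0.50 | 0.66 |
| 1 SD | 0.5 + 0.5 × 1 = 1.00 | about 46% | 0.50 | 0.68 |

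The average loss is 0.75 − 0.66 = 0.09 SD and 1.00 − 0.68 = 0.32 SD. The larger losses of 0.25 and 0.50 SD occur only in the trials where the rule fires.

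**The case against.** A reader might infer that the drinking covariate is an on-treatment variable and that the PL effect will therefore be biased. The documents do not support that. The word weekly describes the evaluation that drinking may affect and does not say when drinking is recorded. No weekly evaluation exists in the visit schedule, so the word may simply be loose. The article implies knowledge of drinking only at entry, through the exclusion criterion, and describes a questionnaire at screening; it describes no collection of drinking during treatment. A baseline reading is at least as plausible, and on that reading there is no bias. Nothing in the article suggests that PL changes drinking. This part of the objection stands, and Step 3 is a conditional illustration only.

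It can also be said that the sentence does not name K-WOMAC or state that analysis of covariance replaces the t test; it might be supplementary. That is fair. K-WOMAC is, however, the only outcome named in the preceding paragraph, so reading the rule as covering it is natural.

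The correlation of 0.7 has no support in the article, and excluding the heaviest drinkers narrows the range of drinking. The gain from adjustment may thus be small. This is also a 24-subject pilot without a power claim, which limits the consequences.

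The remaining argument, that such detail belongs in an unseen analysis plan, does not remove the point. The article states the trigger outright. An analysis plan that follows it keeps the fault, and one that does not would contradict the protocol.

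**Conclusion.** The concern holds as a point about a data-dependent and incompletely specified rule. If drinking is a baseline value, the estimate is unbiased. The cost is a model chosen by the data, a mildly conservative test, and the loss of whatever precision planned adjustment would bring: 8 percentage points of power at correlation 0.5 (54 − 46) and 24 at 0.7 (70 − 46) for a 1 SD effect. At correlation 0.3 or below there is little or nothing to gain. These figures rest on the assumed 5% trigger, the assumed correlations and a single 8 vs 8 comparison.

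Attenuation of the PL effect needs three things together: on-treatment measurement, an effect of PL on drinking, and the rule firing. The article establishes neither of the first two, so bias should not be claimed as a finding. The wording leaves the possibility open, and fixing the covariate at baseline closes it. The change is worth making because it is cheap, although the stakes in this pilot are modest.

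**What to change.** Delete the condition that makes adjustment depend on a group difference. Name the covariates of the K-WOMAC comparison in advance, from baseline values only, and keep them whatever the observed balance. The candidates are baseline K-WOMAC, which section 2.9 already has measured, and baseline drinking only if the sponsor believes it prognostic. Adding baseline K-WOMAC is a recommendation beyond the minimum repair. Report drinking during the trial by arm descriptively and keep it out of this model.

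The cost is one sentence and 1 df per covariate. In an 8 vs 8 comparison the residual df fall from 14 to 13 with one covariate and to 12 with both. If a covariate turns out not to be prognostic, power falls slightly: from about 46% to 43% for a 1 SD effect with one covariate at correlation 0.
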